### **13. ALTERNATIVES TO STUDY PARTICIPATION**

The alternatives to participation in this study are to not participate and to seek treatment with another therapist or community program.

### **14. POTENTIAL RISKS**

1. Degree of inconvenience for Veterans who may miss work, activities, meetings, etc. to participate in the study
2. Potential risk of psychological assessments. For some participants, disclosing potential information about mental health symptoms and eating behaviors may be uncomfortable. Questions regarding individual behaviors, emotions or attitudes may be considered sensitive to some participants.
3. Potential risk of psychological treatment. As in all therapies, treatment for binge eating and weight may encourage discussion of sensitive or distressing topics which may provoke emotional responses for some participants. The ROC treatment involves exposure to food while restricting consumption of said food. This may provoke negative emotions for some participants. Further, participants in some treatment arms will be encouraged to increase their level of physical activity. Improper or too-vigorous exercise or physical activity, if performed by the participant against the advice of the research staff, could be associated with injury or discomfort.
4. Potential risk of loss of confidentiality: Risk associated with breach of confidentiality of behavioral research data. Since this study includes psychological assessments as well as height and weight, there is the potential that this information might not be kept confidential (for instance by theft of study material).

### **15. RISK MANAGEMENT PROCEDURES AND ADEQUACY OF RESOURCES**

*There is a degree of inconvenience for Veterans who may miss work, activities, meetings, etc. to participate in the study.* It is possible that missed work could result in decreased income. At CHEAR, assessments are conducted in the morning, afternoon, evening and on Saturdays if necessary to reduce the impact of assessments on Veteran's work or activities. Participants will be made aware of the weekly treatment night during the screening process. If a Veteran is busy with activities or other commitments on that evening, they will be offered to wait for another cohort which will be offered on an alternative evening.

*There is a risk of reactivity to assessment procedures.* For some participants, disclosing information about mental health symptoms and eating behaviors may be uncomfortable. Questions regarding individual behaviors, emotions or attitudes may be considered sensitive to some participants. This risk will be mitigated by having well supervised assessors conduct the assessments, thereby being aware of emotional reactivity or stress response in an early form. Veterans will be notified that they may decline to answer any questions due to discomfort or may choose to end their participation in screening if no longer interested.

*Risk management for psychiatric concerns identified in assessment*

For any unidentified/unreported psychiatric concerns identified during assessments for this project, we will execute the following protocol:

- The Veteran will be notified of concerns identified.
- The Veteran will be given a list of referrals in the community or referred back to the VASDHS mental health team (depending on source of recruitment). [name] and [name] are both licensed clinical psychologists, and experienced in assessing psychiatric risk. CHEAR has an extensive list of community mental health referrals, some which offer treatment at no or low-cost.
- If significant concern is warranted (i.e. active suicidal ideation, risk of intent to hurt self or others), participants will be immediately assessed by a licensed clinical psychologist at CHEAR (of which there are 5 at this time), and an appropriate psychiatric referral will be made. Should any imminent concerns be present and a participant's safety cannot be guaranteed, [name] or another licensed psychologist at CHEAR will call the Psychiatric Emergency Response Team (PERT). PERT consists of specially trained officers and deputies who are paired with licensed mental health professionals. Together, they respond on-scene to situations involving people who are experiencing a mental health related crisis and can initiate involuntary hospitalization and provide crisis management as necessary.

*There is a risk of reactivity to treatment procedures.* As in all therapies, treatment for binge eating and weight may encourage discussion of sensitive or distressing topics which may provoke emotional responses for some participants. This risk will be mitigated by having well supervised interventionists conduct the treatments, thereby being aware of emotional reactivity or stress response in an early form, and conducting treatment in such a way as to reduce such responses. Should a participant become symptomatic during treatment, the interventionist will assess the problem, and in consultation with [name] and [name], decide whether to withdraw the individual from treatment and/or to refer them for treatment elsewhere. Participants will be encouraged to talk to their group leaders, study coordinator or the principal investigator if they experience distress in treatment. Participants will be reminded they can withdraw their participation at any time without consequence. If any staff member at CHEAR has concerns that participation in treatment is negatively affecting a participant, the staff member will discuss the case with [name] and/or [name] who can meet with the participant and make the decision to withdraw participation of any participant from the study without their consent if it is in their clinical best interest. All participants who are withdrawn will be provided referrals in the community and/or referred back to their mental health provider.

*There is a risk of injury.* In the ROC arm, Veterans will be encouraged to increase their physical activity. Although research staff will help tailor the physical activity recommendations to a Veteran's physical or medical status, it is possible that improper or vigorous physical activity could be associated with injury or discomfort. In order to address this risk, Veterans will self-report orthopedic problems, gait disturbances, and medical status prior to enrolling in the study. All participants will be instructed to alert the research team of any injury sustained as soon as possible. If an injury has occurred, we will request that the participant follow-up with his/her primary care provider before continuing with the physical activity recommendations in the study.

*Risk of loss of confidentiality as a direct result of participation in the recruitment, screening, assessment and treatment.* There is a very small risk that identified data may be compromised as part of this study. All data collected during the study assessments or treatment is de-identified and only labeled with an ID number, no name or other identifying information. With regards to paper forms, consent forms with identifying information are stored in a locked room in a locked filing cabinet. Hard copies of de-identified data is stored in a separate locked room in a locked filing cabinet. Any electronic document with identifiable information is password protected and the password is only provided to essential study staff who need to access that document to aid in the conduct of the study. Electronic de-identified data is stored on encrypted firewall protected UCSD servers or on REDCAP and only accessible by study staff. Participants will not be identified in any reports or publications. Appropriate parties other than the UCSD research staff may be granted access to the study data as required (e.g., the sponsor of this study, the Department of Defense, UCSD IRB personnel, medical monitors, or other similar entities); these individuals will be bound by the same rules of confidentiality as the investigative team not to reveal the participant's identity to others. The only time confidentiality will purposefully be broken is when required by law if the study team receives information that a participant is a threat to him/herself, another specified target, or regarding actual or reasonably suspicious child, dependent adult, or elderly abuse or neglect.

There is a risk that a Veteran may know another Veteran in the waiting room or treatment group. We have experience managing this kind of loss of confidentiality. Both participants will be reminded of the confidentiality

expectations in a treatment study, and will meet with trained CHEAR staff individually to assess participant concerns. This method has been successful to date in our other studies, and most times, participants are not concerned about individual they know. If a Veteran has concerns about a familiar individual, the Veteran with the concern will be offered an option to participate in a future cohort.

For the transfer of screening data from the VASDHS staff to the UCSD CHEAR recruitment staff, a separate IRB will be filed under the VA to cover the consent and HIPAA exceptions of the pre-screening process of Veterans at the VA and any information used to determine eligibility. These forms will give permission for [name] team to share the names and screening data with UCSD CHEAR study staff. [name] team will provide copies of the screening data either on a password-protected document electronically or on a password protected cd with names and contact information stored separately linked to an ID. Only the VASDHS staff and the CHEAR recruitment staff will have the password to unlock the CD or files. The VA will securely store the electronic data according to VASDHS IRB and policies as well as securely keep the consent forms in locked filing cabinets in which only the VASDHS study team will have access to them.

To help maintain confidentiality of participants, if emailing more than one participant (e.g., emailing about reminder for treatment session), all participant's email addresses will be kept confidential by using the BCC function and no participant names will be included. When emailing participants from email templates, staff will copy from our templates instead of forwarding from emails sent to other participants and to always start new e-mail documents to ensure no participant email information is accidentally disclosed to another participant.

**Data Safety and Monitoring (DSM):** Because of this low risk status, the data and safety monitoring plan (DSMP) for this trial focuses on close monitoring by the principal investigator (PI) in conjunction with a safety officer, along with prompt reporting of excessive adverse events and any serious adverse events to the DoD and to the IRB at the University of California San Diego. The safety officer for this trial will be [name]. [name] is a psychiatrist with over 30 years of experience in the assessment and treatment of patients with eating disorders and obesity in research trials and in clinics. [name] is a Professor at the University of Minnesota, Psychiatry Department and the Medical Director of the Emily Program in Minnesota. As a Safety Officer, [name] will review the reports sent by the study coordinator (at the frequency outlined below) and will use a checklist to determine whether there is any corrective action, trigger of an ad hoc review, or stopping rule violation that should be communicated to the study investigator, the University of California San Diego IRB, and the funding agency.

Safety reports will be sent to [name] (statistician), [name] (Principal Investigator), and the safety officer ([name]). The Project Coordinator will be responsible for assembling the data and producing these reports, as well as assuring that all parties obtain copies of these reports.

The frequency of data review for this study differs according to the type of data and can be summarized in the following table:

| Data type                                                                                    | Frequency of review                 |
|----------------------------------------------------------------------------------------------|-------------------------------------|
| Subject accrual (adherence to protocol regarding demographics, inclusion/exclusion)          | At the end of each recruitment wave |
| Adverse event rates (injuries)                                                               | Quarterly                           |
| Stopping rules report regarding statistical power implications of drop outs and missing data | Yearly                              |

**Stopping rules:** In this minimal risk intervention trial, it is more likely that drop-outs or difficulty in recruiting adequate numbers of participants will require stopping the trial, than that of excess adverse events will occur and require stopping the trial. However, as outlined elsewhere, we will monitor injury rates in all participants and the safety officer, together with the study investigators, will alert the IRB and the DOD if a larger than reasonably expected injury rate should occur in the treatment group.

**Measurement and reporting of adverse events.** Serious adverse events will be those that result in death, are life threatening, require (or prolong) hospitalization, cause persistent or significant disability/incapacity, result in congenital anomalies or birth defects, or are other conditions which, in the judgment of the investigators, represent significant hazards. Serious adverse events will be reported by the PI verbally and in writing as soon as possible to the IRB and

as appropriate to the DoD. Adverse events will be those that include any unfavorable and unintended diagnosis, symptom, sign, syndrome or disease which either occurs during the study, having been absent at baseline, or, if present at baseline, appears to have worsened. All adverse events (serious and non-serious, expected and unexpected) will be reported to the UCSD IRB at timelines according to appropriate guidelines (e.g., expected and not study related at IRB continuing review; unanticipated problems involving risk to participants within 10 working days) and reported to the study monitor quarterly if anticipated and not study related, or within the same timeline as reporting to the IRB if sooner than quarterly. All unanticipated problems involving risk to subjects or others will be promptly reported to the UCSD IRB and the DoD.

Blinded adverse events data will be presented to the study statistician, the PI, and the safety officer throughout this trial. The adverse event log will be used by the study staff to report injuries that may be associated with this intervention. Very few injuries are expected, as the main focus of treatment is changing eating behavior. The physical activity recommendations will include both vigorous and lifestyle physical activities, which can be adapted to the Veteran's physical or medical status.

It is not likely but should any adverse events occur during screening at the VASDHS they will submit those to the VASDHS IRB and follow all protocols and report to the DoD and DSMP as appropriate.

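### The quarterly adverse-event rate, the event log and the only spelled-out safety alert are worded as injuries, while the protocol's own definition and reporting duty cover all adverse events

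*Protocol*

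**What the plan says.** Four places in Protocol Section 15 are worded for injuries:

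- The review-frequency table under Data Safety and Monitoring: "Adverse event rates (injuries", reviewed quarterly. The bracket closes after that word.
- The log, under Measurement and reporting of adverse events: "The adverse event log will be used by the study staff to report injuries that may be associated with this intervention".
- The monitored rate, under Stopping rules: "we will monitor injury rates in all participants".
- The alert to the IRB and the funder, in the same sentence: "if a larger than reasonably expected injury rate should occur in the treatment group".

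Other places are wider:

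- The definition in Section 15: "Adverse events will be those that include any unfavorable and unintended diagnosis, symptom, sign, syndrome or disease". The event must be new since baseline or worse than at baseline.
- The reporting duty in Section 15: all adverse events, serious or not and expected or not, go to the UCSD IRB and to the study monitor, quarterly or sooner. Blinded adverse event data go to the statistician, the PI and the safety officer throughout the trial.
- The opening of the Data Safety and Monitoring paragraph: excessive adverse events are to be reported promptly, with no limit to injuries.
- The risk list in Section 14: emotional responses can occur in any therapy, and for one arm specifically, "The ROC treatment involves exposure to food while restricting consumption of said food. This may provoke negative emotions for some participants".
- The handling of distress in Section 15: "Should a participant become symptomatic during treatment, the interventionist will assess the problem". Referral or withdrawal from treatment may follow.

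**The concern.** A monitoring plan needs its definition, its recording tool, its tabulated rate and its alert to cover the same events. Here the definition and the reporting duty cover everything, while the recording tool, the rate and the detailed alert are described for one type of event. Section 15 itself expects very few injuries, because treatment is mainly about changing eating behavior.

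At stake is whether the quarterly rate means what its label suggests. A reader of that row could take it as the adverse event rate of the trial, when as worded it is the injury rate. Staff told that the log is for injuries have no stated place to record a new or worsened psychological symptom. Two people applying the plan in good faith could therefore produce different counts.

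**Working it through.** No arithmetic applies. The protocol gives no expected adverse event rate and no numeric threshold. The check sets the parts of the safety plan side by side.

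| Element | Where | Scope as worded |
|---|---|---|
| Definition of adverse event | Section 15, Measurement and reporting | All events |
| Duty to report to IRB and study monitor | Section 15, Measurement and reporting | All events |
| Blinded data to statistician, PI, safety officer | Section 15, Measurement and reporting | Not limited |
| Prompt reporting of an excess | Section 15, Data Safety and Monitoring, opening | Not limited |
| Log | Section 15, Measurement and reporting | Injuries |
| Quarterly rate | Section 15, frequency table | Injuries |
| Monitored rate and alert | Section 15, Stopping rules | Injuries |

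1. **Does the definition reach psychological harm?** Yes by breadth, though not by name. A new or worsened symptom or diagnosis qualifies if it is unfavorable and unintended. Passing discomfort during a planned food exposure may not qualify, because some reaction is part of the exercise. Distress that leads staff to withdraw a participant is a much clearer case.

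2. **Does the plan anticipate such events?** Yes. Section 14 lists them, and Section 15 describes assessment, referral and withdrawal by staff. Neither section says that they are logged or counted.

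3. **Do they enter the quarterly rate?** Not as worded. Whatever the number of non-injury events in a quarter, their contribution to a row restricted to injuries is zero. The other two rows of the table cover accrual and a yearly report on the power implications of drop-outs and missing data. A withdrawal for distress might be counted there as a drop-out, but not as an adverse event.

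4. **Is there another route to the reviewers?** Yes: the all-event reports and the blinded adverse event data. Three details are left loose. The safety officer is said to review reports at the frequencies in the table, and its only adverse event item is injuries. The recipient of the quarterly all-event reports is called the study monitor, a role that Section 9 (Delegation of Responsibilities) assigns to UCSD and not clearly to the safety officer. The only log described as a source is the one for injuries.

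5. **Does a listed modification settle it?** No. The modifications at the end of the protocol do not touch the safety table, the log or the alert.

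**The case against.** The strongest reply is that the injury wording is narrow only in places. The sentence on the log says that it is used for injuries, not that it is used for nothing else. A duty to report all adverse events presupposes that they are recorded. The safety officer receives adverse event data without an injury limit, works from a checklist that is not described as limited to injuries, and is a psychiatrist experienced in eating disorders. Injury is also a sensible item to tabulate, because Table 1 prescribes physical activity in ROC and none in CBT. So it cannot be said that the table ignores risks specific to ROC.

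Most of this stands, and it rules out two stronger readings that a reader might infer. One is that an excess of psychological events would be invisible to reviewers. The documents do not support that, because the all-event reports and the safety officer's data remain open. The other is that the trial could not describe psychological safety by arm. PHQ-9 and GAD-7 are scheduled in both arms at baseline, mid-treatment, post-treatment and 6-month follow-up (Table 2), and Primary Aim 1 compares time to dropout between arms. Nor would a wider quarterly table by itself show a difference between arms, since the adverse event data are presented blinded.

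The reply does not remove the mismatch. Individual reports are not a rate, and the plan promises to act on an excess of adverse events but spells out how only for injuries. If all events were meant, the bracket in the table is wrong. If only injuries were meant, the rate is narrower than the plan's own definition.

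**Conclusion.** The safety section is inconsistent with itself. The single tabulated adverse event rate, the log and the only spelled-out alert are worded as injuries. The definition and the reporting duty cover all events, and the risk list includes psychological reactions, one of them tied to ROC food exposure. As written, non-injury events have no stated log and do not count in the quarterly rate, although they can reach reviewers by other routes.

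This is a modest point for a trial that the protocol treats as low risk, but worth correcting because it concerns safety monitoring and costs almost nothing. It rests on two readings: that the bracket limits the row to injuries and is not merely an example, and that the log sentence describes the log's intended content. If the sponsor meant either more widely, the change only makes the text say so.

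**What to change.** In Protocol Section 15:

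- Change the quarterly row to rates of all adverse events as the section defines them, tabulated by type: injury, psychological, other.
- Word the log so that it records all adverse events, including distress that leads to withdrawal by staff.
- Reconcile the injury-only monitoring and alert wording under Stopping rules with the promise, at the start of Data Safety and Monitoring, to report excessive adverse events. No threshold is proposed here; that is for the sponsor and the safety officer.
- State whether the study monitor who receives the quarterly all-event reports is the safety officer.

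Optionally, add PHQ-9 and GAD-7 summaries to the safety report, since both are already collected.

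The cost is a few sentences and a few more rows in an existing quarterly report, with no new assessments or staff.

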| Physical activity prescription | Physical activity is used to help regulate physiological and psychological responding to food cues.                                                                                                                                                                          | None                                                                                  |
| Goal setting                   | Goal setting focuses on self-monitoring and practicing mastery and toleration of physiological /psychological arousal, as well as food intake and physical activity                                                                                                          | Goal setting focuses on self-monitoring of food intake, thoughts and behaviors.       |
| Coping skills                  | Methods for managing psychological and physiological arousal. Discussed each week in regards to mastery and toleration of physiological /psychological arousal.                                                                                                              | Cognitive restructuring, stress management, behavior chains to reduce binge eating    |

(total treatment duration = 5 months, 18 meetings). Descriptions of the treatment arms follow and key differences between the treatment arms are outlined in Table 1. All treatment sessions will be audiorecorded for supervision and fidelity purposes.

**Regulation of Cues (ROC).** The ROC program provides psychoeducation, coping skills, self-monitoring and experiential learning. Physical activity will be promoted to improve self-regulatory strength and to help participants master and tolerate physiological and psychological arousal, resist cravings and overeating.

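### The injury alert is tied to an unnamed 'treatment group' in a trial with two active arms; read as ROC, it sits badly with blinded adverse event review (minor, participant protection only)

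*Protocol*

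**What the plan says.** All of the safety text is in protocol section 15.

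- **Scope and trigger (Stopping rules).** The monitoring covers everyone: "we will monitor injury rates in all participants and the safety officer, together with the study investigators" are to alert the IRB and the Department of Defense. The trigger is narrower: a "larger than reasonably expected injury rate should occur in the treatment group". No expected rate or limit is given.
- **Blinding (Measurement and reporting of adverse events).** "Blinded adverse events data will be presented to the study statistician, the PI, and the safety officer throughout this trial".
- **Distribution (Data Safety and Monitoring).** Safety reports go to those same three roles. The project coordinator assembles them and is responsible for "producing these reports, as well as assuring that all parties obtain copies of these reports". Injury rates are reviewed quarterly.
- **Where the hazard lies.** The paragraph on injury risk says "In the ROC arm, Veterans will be encouraged to increase their physical activity". In Table 1 (Treatment Arms), the ROC entry under physical activity prescription reads "Physical activity is used to help regulate physiological and psychological responding to food cues", and the CBT entry is none.
- **Expected frequency.** "Very few injuries are expected, as the main focus of treatment is changing eating behavior".
- **Other routes.** The monitoring plan includes "prompt reporting of excessive adverse events and any serious adverse events". All adverse events are reported to the IRB, and the safety officer may trigger an ad hoc review.

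**The concern.** The alert is the protocol's stated check for an excess of injuries caused by the intervention. To act on it, the people responsible must know whose rate to look at and must be able to see that rate. The trigger names a single treatment group in a trial of two active treatments. If it means ROC, the reviewers are asked to judge a rate that blinded reports do not show them. If it means everybody treated, they can see the rate, but half of the people in it were given no activity advice. Either way, an excess of ordinary injuries confined to ROC is less likely to reach the IRB and the funder. What is at stake is participant protection; no efficacy or feasibility estimate depends on it.

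**Working it through.** The protocol gives no expected injury rate, limit or false-alarm level, so there is no figure to reproduce. The point is first one of wording; the arithmetic only gives it a size.

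**1. What the trigger can mean**

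| Reading | Support | Consequence |
|---|---|---|
| The ROC arm | Injury paragraph in section 15; Table 1 | Conflicts with blinded data: no arm-level report and no unblinding step is described |
| Everyone treated, both arms | Monitoring covers all participants | No conflict, but a ROC-only excess is diluted |
| A session group of up to 20 | The phrase is used this way under Treatment Arms and in the confidentiality text of section 15 | Implausible as an alert unit |

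The protocol does not say whether blinded means pooled or split into coded arms A and B. With coded arms a difference would be visible, but no step attributes it to ROC.

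**2. Dilution.** Assume equal arms (no allocation ratio is stated), CBT at the expected rate p0 and ROC at R × p0. The pooled rate is (R × p0 + p0)/2 = p0 × (R + 1)/2. For R = 2 this is 1.5 × p0; for R = 3 it is 2 × p0.

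**3. Chance of an alert (illustration).** Inputs: at least 120 randomized (Research Design), taken as 60 per arm; p0 assumed to be 5%, 2% or 1%; each participant counted once; one look. The limit c is the smallest count with probability at most 0.05 when both arms have risk p0.

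- ROC count: P[Bin(60, R × p0) ≥ c].
- Pooled count: P[Bin(60, R × p0) + Bin(60, p0) ≥ c].

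| p0 | Limit, ROC (false alarm) | Limit, pooled (false alarm) | R = 3: ROC v pooled | R = 2: ROC v pooled |
|---|---|---|---|---|
| 5% | 7 (0.030) | 11 (0.038) | 0.815 v 0.667 | 0.394 v 0.289 |
| 2% | 4 (0.032) | 6 (0.034) | 0.489 v 0.348 | 0.219 v 0.153 |
| 1% | 3 (0.022) | 4 (0.033) | 0.269 v 0.220 | 0.119 v 0.107 |

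**4. Small counts.** With fewer participants or rarer events, the discrete limits dominate and the order can reverse.

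- 20 per arm, p0 = 5%, R = 3: ROC ≥ 4 gives 0.352, pooled ≥ 5 gives 0.371. The false-alarm rates are 0.016 and 0.048.
- 40 per arm, p0 = 1%, R = 3: 0.118 v 0.215, with false-alarm rates 0.007 and 0.047.

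These reversals come from the unequal false-alarm rates. Bringing each rule to exactly 0.05 means alerting with probability g = (0.05 − attained)/P(X = c − 1 under p0) when the count is one below the limit. In the first case, for the ROC count, g = 0.0341/0.0596 = 0.572, and the chance becomes 0.352 + 0.572 × 0.243 = 0.491. The pooled count treated the same way gives 0.375. In the second case the matched values are 0.294 and 0.222.

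**5. An equal trigger on either arm.** Give both arms a common limit with overall false-alarm probability at most 0.05, at 60 per arm.

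- p0 = 5%, limit 8 (0.019): 0.698 for R = 3 and 0.256 for R = 2.
- p0 = 2%, limit 5 (0.014): 0.296 for R = 3 and 0.098 for R = 2.

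Three of these four values are below pooled review, and the fourth gains only 0.698 − 0.667 = 0.031. The gain at these rates therefore needs a trigger specific to ROC.

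**The case against.** **The conflict depends on the reading.** The sentence opens with all participants, about 300 people consent for 120 treated, and screening events are handled separately, so the phrase may simply mean those treated. This stands in part: on that reading nothing contradicts the blinding. The phrase remains ambiguous, though, and a ROC-only excess is still diluted.

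**Protection does not rest on this sentence.** This stands, and it limits the point. Excessive and serious events are promptly reported without regard to arm, all adverse events go to the IRB, and the safety officer can call an ad hoc review. An injured participant is asked to see a primary care provider before resuming activity recommendations, which are ROC content. Case review may therefore point to ROC, although it yields no rate for that arm.

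**The numbers rest on assumptions.** This also stands. The rates, equal arms and the 5% false-alarm limit are not in the protocol, whose standard is judgement. At 1% the advantage at 60 per arm is small.

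**Stronger readings.** A reader might infer that the alert cannot work at all, or that participants are left unprotected. The documents do not support either: pooled or coded review weakens the alert without disabling it, and the other routes remain. Nor does anything suggest bias in the comparison of ROC with CBT.

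**Conclusion.** The point holds as a minor one. The trigger names neither active arm. On its natural reading it asks three blinded roles to judge a rate that the protocol does not give them; on the alternative reading a ROC-only excess is diluted, with a doubled rate appearing as 1.5 times the expected one. In the illustration at 60 per arm, a tripled ROC rate is flagged with probability 82% v 67%, 49% v 35% and 27% v 22% (ROC v pooled count) for expected rates of 5%, 2% and 1%. These figures assume equal arms, CBT at the expected rate, a single look and at most 5% false alarms. At lower enrolment or with rarer events, no firm size can be given. The effect is confined to participant protection in a trial where few injuries are expected.

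**What to change.** 1. Under Stopping rules in section 15, make the alert refer to the ROC arm, with CBT as the comparison, and keep overall injury monitoring in all participants. Do not substitute an equal trigger on either arm.
2. Have the data manager, who conducts the randomization and has no contact with participants, send the safety officer alone a quarterly injury table by arm. Under Measurement and reporting of adverse events, keep the PI and statistician blinded unless the safety officer calls an ad hoc review. The table is then shared, so that the safety officer and investigators can raise the alert together as the protocol requires.
3. Under Data Safety and Monitoring, exempt this table from the rule that every party receives copies.

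Whether a rate is higher than reasonably expected remains the safety officer's judgement; the limits in the illustration are not proposed as rules.

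Cost: a few sentences in section 15 and one extra table per quarter, with no new data, committee or numeric boundary. The downside is that the safety officer is unblinded to arm, but the protocol gives that role no treatment or assessment duties.
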